# Study Protocol

# Title: Randomised controlled feasibility trial evaluating the effectiveness of mindfulness compared to exercise and mindfulness on fatigue in women with gynaecology cancer.

Gynaecology Exercise and Mindfulness Study (GEMS)

Intervention protocol

Section 1 Background and rationale.

Introduction

Gynaecology cancer encompasses ovarian, endometrial, cervical, vaginal, vulva, fallopian tube, and placenta (Lin *et al.* 2016). In the United Kingdom (UK) 21,493 new cases of gynaecological cancer are diagnosed every year (*Gynaecological Cancer Research Charity.* 2020). Treatment modalities can be effective in managing and treating these cancers but may lead to unwanted long term side effects. One side effect is fatigue, the prevalence of which, for all types of cancer, was identified as 52% and for the gynaecology cancer population, this varied between 17-33% with many reporting to experience cancer related fatigue (CRF) many years after treatment (Sekse *et al.* 2015; Ma *et al.* 2020; Sheehan *et al.* 2020a). It has been described not only as a physical sensation but also has emotional and cognitive symptoms suggesting that it is multi-dimensional (McMillan and Newhouse 2011; Coleman *et al.* 2012; de Raaf *et al.* 2013; Dennett *et al.* 2016). To date, few studies evaluate interventions that target all dimensions of fatigue suggesting a multi-modal approach that addresses all aspects is required.

Mechanisms.

Risk factors for CRF that have been described, include depression and insomnia suggesting that the presence of these are not only possibly correlated but may also have an impact on the levels and severity of CRF (Bower 2014). Indeed, the term ‘symptom cluster’ has recently been adopted to describe this and the most common symptoms in this cluster have been identified as depression, insomnia, and fatigue (Payne *et al.* 2008; Oh and Seo 2011; Joly *et al.* 2019). Which suggests that managing fatigue would require the incorporation of interventions that deal with the multiple symptoms of depression, insomnia, and fatigue collectively (Bower 2014; Naraphong *et al.* 2015; Poort *et al.* 2020).

Existing Knowledge

There has been much research conducted that has shown a positive effect of exercise with regards to CRF (Wang *et al.* 2011; Keogh and MacLeod 2012; Cramp and Byron‐Daniel 2012; Zou *et al.* 2014; Tian *et al.* 2016; Juvet *et al.* 2017; Schuler *et al.* 2017; Mugele *et al.* 2019). A number of randomised controlled trials have shown that exercise can result in improvements in CRF (Mock *et al.* 2005; Donnelly *et al.* 2011; Wenzel *et al.* 2013; Zhang, Qi *et al.* 2018). However, the effect of exercise on CRF and quality of life (QOL) remains ambiguous (Velthuis *et al.* 2010; Lin *et al.* 2016). Some cancer studies have reported that the impact of interventions, such as exercise, have shown a positive outcome on CRF and QOL and others have demonstrated no change in either CRF or QoL (von Gruenigen *et al.* 2009; Donnelly *et al.* 2011; Moonsammy *et al.* 2013; Smits *et al.* 2014; Basen-Engquist *et al.* 2014; Mizrahi *et al.* 2015; Al Maqbali 2019). This concept that exercise may not improve all dimensions of QOL or CRF suggests that exercise alone may not be enough to ameliorate fatigue and improve QOL and a multidimensional approach may be required.

Despite the evidence of the positive effect of exercise on CRF, adherence to exercise remains a problem with less than 20% of women with ovarian cancer exercising (Joly *et al.* 2019). Barriers that have been identified for non-participation include time, cost, weather, side effects of treatment or exercise, social aspects, not being aware of guidelines, fatigue, and psychological barriers such as motivation (Hardcastle *et al.* 2018; Lavallee *et al.* 2018). In contrast, the facilitators to exercise that are identified were improved physical and mental wellbeing, decreased feelings of stress, enjoyment, satisfaction, and control over health (Blaney *et al.* 2013; Gho *et al.* 2014; Clifford *et al.* 2018). Understanding what barriers and facilitators are perceived by patients may be required to engage patients with exercise and change lifestyle behaviours. The current behavioural change methods follow models such as the COM-B (Capability, Opportunity, Motivation, and Behaviour). This model denotes that for a behaviour to change 3 aspects are needed; capability, opportunity, and motivation are required. The COM-B is a hub that sits within the Behaviour Change Wheel (BCW) which was synthesised from previous frameworks and enhances the development of behavioural interventions (Cowdell and Dyson 2019; Howlett *et al.* 2019). Interventions that may have begun to identify an approach that addresses some of these psychological barriers such as motivation and that may open a path to consider changing lifestyles, are mindfulness-based (Lucas, A. R. ( 1 ) *et al.* 2017; Cohen *et al.* 2019).

Mindfulness is the practice of intentional awareness in the present moment without judgement. Its practice encourages participants to develop an awareness of current emotions and thoughts with compassion and kindness and will lead to better control of cognition, emotion, and behaviour (Park *et al.* 2020). Research in cancer demonstrates the positive effects of mindfulness on both CRF and QOL and recommend it as an intervention (Leydon *et al.* 2012; Van Der Lee, and Garssen 2012; Lengacher *et al.* 2012; Bruggeman-Everts *et al.* 2015; Johns, S. A. *et al.* 2015; Huang, H. -. *et al.* 2016; Johns, S. A. *et al.* 2016; Lengacher *et al.* 2017; Reich *et al.* 2017a; Zhang, Qiuxiang *et al.* 2019; Xie *et al.* 2020; Xunlin *et al.* 2020; Park *et al.* 2020). Though some of the effect sizes shown in studies were small and did not reach minimal clinical significance, there was still however an effect on psychological distress, which is defined as an emotion that is not pleasant (Cramer *et al.* 2012; Haller *et al.* 2017; Cillessen *et al.* 2019). This effect on the psychological distress and particularly on the symptoms of anxiety, depression, sleep, stress, and quality of life have been shown to significantly improve following the introduction of mindfulness (Carlson and Garland 2005; Huang, J. and Shi 2016; Reich *et al.* 2017b). Some of these symptoms are also present within the ‘cluster symptoms’ previously identified suggesting that there may also be an improvement in fatigue alongside these symptoms.

Need for a trial

Most of the current studies that involve exercise or mindfulness for the management of CRF and psychological distress tend to be in the breast cancer population making it difficult to generalise findings to other cancer populations (Brandenbarg *et al.* 2018; Stelten *et al.* 2020). It would appear that both exercise and mindfulness have individually as interventions demonstrated positive effects on CRF, anxiety, depression, and sleep. Whether mindfulness and indeed adding mindfulness to an exercise regime for managing fatigue in women with gynaecology cancer is of benefit, is yet to be explored. Therefore, this study will aim to assess how feasible and acceptable the interventions, mindfulness, and exercise, will be and if there is any effect on fatigue for the gynaecology cancer patient.

Primary Aim

To explore the feasibility of conducting an 8- week online mindfulness and home-based walking and strength training programme for the management of cancer related fatigue in women with gynaecology cancer. The following objectives will assess feasibility outcomes:

1. To assess participant intervention adherence, study retention and attrition rate.
2. Explore the acceptability of using an online platform for the delivery and data collection of the exercise and mindfulness programme.
3. Explore the perspectives of participants concerning satisfaction (eg the intervention and its’ delivery) perceived value, barriers and facilitators of the online programme.

Secondary aim

To evaluate the effect of an 8 week exercise and mindfulness programme on cancer related fatigue as a primary clinical outcome and the effect on anxiety, depression, sleep and QoL as a secondary clinical outcome in an online setting.

Section 2 Methods

Study design

The study design and development have been reviewed and feedback considered from 2 patient and public involvement representatives.

This design will involve 2 parts firstly, an intervention part which is designed as an open, randomised, control trial with 1:1 allocation to either the mindfulness only group or the exercise and mindfulness group.

Following the intervention the second part will be online focus groups which will be conducted with participants once they have completed the intervention.

Study setting

Both parts of this study, intervention and focus groups, will be conducted online via a web-based, mobile application interface. Participants will be notified that data usage with this app will be minimal and battery usage of mobile devices may increase requiring additional charging of device. Therefore, participants should not incur any additional financial burden.

Participants & Eligibility

Eligibility criteria:

Inclusion criteria:

1. Women >18 years old and able to speak and read English.
2. Diagnosed with stage I-IV gynaecology cancer including endometrial, ovarian, cervical, vaginal, vulva, fallopian tube.
3. A minimum of 3 months post-treatment and up to 5 years.
4. Experiencing fatigue and at screening have a numerical rating score of $\geq$4 on a scale of 0-10.
5. Currently sedentary (exercising < once a week for 20 minutes at a vigorous intensity or, two times per week for 30 minutes at moderate intensity or < 20 minutes three times per week, for the past 6 months).
6. Ambulatory and without the use of a walking aid.
7. Capacity to give informed consent.
8. Access to computer/tablet/smartphone.
9. Access to internet.

Exclusion criteria:

1. Currently actively and regularly practising mindfulness.
2. Have a confirmed diagnoses of Schizophrenia spectrum disorder, Bipolar disorder, Post-traumatic stress disorder, or risk factors for psychosis (eg personality disorder) as participation in a mindfulness program is contraindicated and maybe detrimental to well-being (Van Dam *et al.* 2018).
3. Have an existing medical condition that may inhibit safe participation in the exercise part of the intervention study.
4. Previously diagnosed with a fatigue-related co-morbid medical condition (i.e. Fibromyalgia, Chronic Fatigue Syndrome, Multiple Sclerosis (MS), Myalgic Encephalopathy (ME), Lupus or Arthritis)
5. Have no e-mail address.
6. Participating in other intervention trials.

Sample size

The sample size for this study is based upon feasibility and review of similar studies. The literature demonstrates that feasibility studies with similar interventions and methodologies within the cancer population recruit on average 40 participants in total (Eyles *et al.* 2015a; Victorson *et al.* 2017; Price-Blackshear *et al.* 2020). Therefore it is anticipated that this study will recruit a total of 40 participants with 20 in each arm of the study.

Procedure & Materials

Recruitment.

This study will adopt the approach of rolling recruitment and once participants have been screened and consented will commence the intervention they have been randomised to. Recruitment will take place through the following charities: Cancer Focus, Macmillan and Action Cancer. These organisations have agreed to contact their service users through social media (Facebook, Twitter, Instagram), leaflet drops and other service providers the organisation provide such as counsellors, clinical nurse specialist, support workers etc (appendix 1). They have also provided written confirmation of their commitment to assist in recruitment for this study (appendix 2).

If participants are interested in the study they can self-refer and a contact number for the researcher will be made available through the leaflets, social media or service providers. Participants can call the researcher for further information and if willing and interested screening for eligibility will be performed by the researcher (appendix 3). Once this is complete and it is established that participants meet the criteria participants will be e-mailed participant information sheet by the researcher (appendix 4) and time given to read and ask any questions regarding this. Participants can contact the research team if they have any further questions. Consent (Appendix 5) will be obtained after participants have been given one week to consider the study. An Qualtrics link to an electronic version of the consent will be emailed to participants.

Randomisation

Participants will be randomly allocated to either group through 1:1 allocation. Participants will be randomly assigned using computer-generated random number tables. A researcher/statistician not involved in treatment delivery or collection of outcomes will generate the random allocation sequence. Concealment of treatment allocation will be by placing individual random assignments into serially numbered sealed envelopes and be held by researcher/statistician not involved in treatment or outcome measure collection.

Participants will be notified of which group they have been allocated to via the e-mail they have supplied. A member of the research team will e-mail the participant with this information.

Data collection methods

Outcome measures

Data collection for outcome measures will be self-report measures using valid and reliable tools for measuring these outcomes. Participants will be asked to complete these assessments following randomisation at baseline and on completion of the programme. At baseline participants will also complete demographic information such as age, cancer type, education, income, and education (appendix 6). All of this will be done via Qualtrics (appendix 7), an e-mail reminder will be sent 2 weeks after the initial invitation if completion has not occurred. Access to intervention will only happen once all baseline assessments have been completed.

The following self-report measures will be used to assess outcomes at baseline and post-intervention (copies and links to Qualtrics of all can be found in appendix 7).

Fatigue- The Functional Assessment of Chronic Therapy- Fatigue (FACIT-F) subscale will be used it is a 13- item questionnaire that uses a 5 point Likert scale and has been validated for use with various types of cancer and treatments (Al Maqbali *et al.* 2019; Carlson *et al.* 2019). The lower the score on this scale indicates the greater the fatigue with scores less than 20 representing severe fatigue and scores greater than 45 as normal (Sheehan *et al.* 2020b)

Quality of life- The Functional Assessment of Cancer Therapy General (FACT-G) is a 28- item rated scale. It assesses physical, social, emotional and functional wellbeing. (Cella *et al.* 1993). Higher scores in this questionnaire indicate better quality of life (Park *et al.* 2020)

The psychological outcomes will be assessed using the Hospital Anxiety and Depression Scale (HADS). (Zigmond and Snaith 1983). This questionnaire has 14 questions, 7 each for assessing anxiety and depression (Spahn *et al.* 2013). A HADS score of greater than 11 is more defining of anxiety and depression, with a reduction of 3 points indicating a clinical improvement (Eyles *et al.* 2015b).

Sleep- The Pittsburgh Sleep Quality Index (PSQI) a 19 items questionnaire that measures 7 domains of sleep scored on a 0-3 scale over 1 month (Buysse *et al.* 1989). The questionnaire gives a score that ranges from 0-21 with the higher the score the worse the sleep quality (Yu *et al.* 2020).

Mindfulness- The 24 item Five Facet Mindfulness Questionnaire Short Form (FFMQ-SF) is a 5 point Likert Scale which assess mindfulness in daily life. It measures 5 sub-scales: observing, describing, acting with awareness, non-judgement of inner experience and non-reacting to inner experience. The higher the score the greater the mindfulness (Compen *et al.* 2015; Johns *et al.* 2016)

Participants exercise behaviour will be assessed using the International physical activity questionnaire short form (IPAR-Q -SF). This questionnaire has 7 questions which assess the intensity, frequency and duration of exercise that participants engaged in over the last week.

Interventions

A brief description of the interventions of exercise and mindfulness can be found in (appendix 8). The operationalise of the COM-B model with the interventions for this study can also be found in (appendix 9).

Outcomes

Primary Outcome

The feasibility and acceptability of the study will be assessed in line with the MRC guidance on Developing and evaluating complex interventions (Craig 2019). These outcomes will assess participants that have completed or take part in the intervention part of the study and will be the following:

1. Adherence- interventions will run over 8 weeks. The completion of 4 weeks for mindfulness and 30min of home-based exercise weekly for two thirds (67%) of the duration of the trial will be regarded as adherence to the program. These levels of adherence are based on previous studies that have used the same levels (Mock *et al.* 2005; Pinto *et al.* 2005; Kim *et al.* 2019; Park *et al.* 2020) This will be assessed through the electronic diaries/logs that participants will be encouraged to complete along with the website/app data information- on frequency and duration of participant engagement with each session.
2. Attrition-We will estimate, following a review of web-based mindfulness intervention studies that the attrition rate will be approximately 20% with 10% to 15% of missing data (Carlson *et al.* 2019; Subnis *et al.* 2020).
3. Time to recruit, recruitment and retention rates, reasons for non-participation and acceptability of data collection. Time to recruit, recruitment and retention rates will be gathered through administrative data during (pre)screening, enrolment, allocation and follow-up. Reasons for non-participation, intervention/study dropouts will be collected when possible. Acceptability of data collection will be retrieved through missing data within questionnaires.
4. Acceptability of the programme will be assessed using focus groups this will include participants experience on the virtual delivery and data collection along with their experience and reflections on the exercise and mindfulness components of the intervention it will be achieved in the following way:

Design

Qualitative data collection utilising online focus groups will be facilitated via the Microsoft Teams (MS Teams) interface. This format for focus group has advantages including less dropout, more relaxed participants resulting in better communication, a more diverse group as able to include participants that are further away and cost-effective (Halliday *et al.* 2021)

Participants

Group sizes can vary and can be between 4 and 12 for focus groups (Barbour 2008). For online focus groups, a more realistic number that has been suggested by the literature would be a maximum of 6 per group (Holloway 2005; Halliday *et al.* 2021). The number and size of groups will also be dependent on trial recruitment numbers and continue until data saturation, which will be reached when no new information is generated (Goei *et al.* 2020). Separate groups will take place for each intervention group to ensure that each group can share and reflect on their similar experience of the intervention they took part in.

Materials

Once participants have completed the 8 weeks of the intervention, they will be invited to take part in online focus groups. An e-mail invitation (Appendix 10) will be sent along with a participant information sheet (Appendix 11) about the focus group. A follow-up phone call will be made by the researcher. Interested participants will be sent a confirmation e-mail outlining a suitable time and date. Confirmation of attendance will be requested along with consent prior to the focus group taking part online. If consent (Appendix 12) has not been received before the focus group, it will still be possible to achieve consent on the day of the focus group. This will be achieved by allowing the participants to enter the online focus group on Microsoft Teams (MS Teams) into a separate room and the consent process will occur before allowing participants to be allowed into the main focus group. A semi-structured interview guide (Appendix 13) shaped by relevant literature was developed which contained open-ended questions that reflected the objectives of the study. Probes will be used to elicit additional information when required. As the groups progress, the prompts will be developed to ensure that the phenomenon is thoroughly explored.

Procedure

Participants who agree to take part will be allocated to groups, these will be mixed groups of age, cancer type and stage but all participants will have completed the same intervention. To ensure that groups retain participants from the same intervention, participants will be asked by the research team through e-mail to provide the research team with information of which group they were randomised to. The allocation of groups will be made by the research team prior to focus groups taking place. If group numbers are too large, small or unevenly distributed then a decision within the research group will be reached regarding on reallocation of participants to groups. Groups will take place as close to the completion of the intervention as is practical. The groups will be facilitated by 3 researchers one of whom will be a facilitator and will ensure that the discussion stays on topic and equal time is shared amongst participants. The other will be responsible for technical support and will support participants during the session, record the session and take notes. The 3^rd^ researcher will be present in case any participant becomes distressed and will need to be removed from the focus group. If participation in these focus groups causes distress for any participants, a distress protocol (appendix 15) is in place to manage this. The PhD researcher, [name], has undertaken training with Ulster University on conducting focus groups but will be supported by [name] and team in undertaking these focus groups. Participants will be informed that the sessions will be recorded and if possible asked to keep audio and video on as this will aid the flow of conversation and will allow the facilitator to take field notes to capture both verbal and non-verbal communication. All focus group discussion will be audio and video recorded, then transcribed verbatim for analysis (Barbour 2008)

Analysis of data from focus groups will be done using Thematic Analysis. This type of analysis is flexible and allows for the in-depth identification and interpretation of themes. (Holloway and Galvin 2016; Castleberry and Nolen 2018) The phases of the analysis will include: familiarising with data, generating initial codes, searching for themes, reviewing themes, defining and naming themes and integrating these themes into a final report for publication (Braun and Clarke 2006).

Secondary Outcomes

Will include fatigue, QOL, sleep, anxiety and depression and mindfulness all of which will be assessed using self-report measures as described earlier.

Participant timeline

Please see Appendix 14.

Timeline for Study

| Task | Months 2021-2023 | | | | | | | | | | | | | |
| --- | --- | --- | --- | --- | --- | --- | --- | --- | --- | --- | --- | --- | --- | --- |
|  | Sep-Dec | | | | Jan-Mar | | Apr- Jun | | Jul-Sep | Oct-Dec | | | Jan-Mar | Apr-Jun |
| Peer review |  |  | | |  | |  | |  |  | | |  |  |
| Filter committee |  |  | |  |  | |  | |  |  | | |  |  |
| UU REC |  | |  | |  | |  | |  |  | |  | |  |
| Mobile App Development |  | | | |  |  |  | |  |  | |  | |  |
| Intervention group recruitment |  | | | |  |  |  | |  |  | |  | |  |
| Focus groups |  | | | |  | |  |  |  |  | |  | |  |
| Data analysis |  | | | |  | |  | |  |  |  |  | |  |

Ethics and dissemination

Ethical approval will be sought from the Nursing/Health Science filter Committee and University of Ulster Research Ethics Committee (UREC).

The findings of the research will be communicated with those who participated in the study either via email or a local event. The researcher will disseminate the projects findings and outputs via oral and poster presentations at local, national and international conferences and publications in peer reviewed journal papers.

Confidentiality

Governance of Data for intervention part of study:

Data will be anonymised, and stored securely. Databases will be encrypted, as will any transferred data. The key to the participant IDs will be held by the Chief Investigator. Access to the anonymised data will use authentication and be traceable by login details.

If a person withdraws from the study their data will kept for 10 years, participants will consent to this (appendix 5). Personal data will only be retained for the duration of the study. Further information on data handling can be found at:

<https://www.ulster.ac.uk/__data/assets/pdf_file/0003/75639/DataHandling.pdf>

This is a self-management project. As such, access to the app will be via download. This app is a protype that will be developed in collaboration with the School of Computing at Ulster University. Pilot testing of this app will take place with the 2 Patient and Public Representatives and an additional 3 service users resulting in 5 testers altogether.

Data from the app will be uploaded securely to a secure server housed in the Data centre at Ulster University Coleraine Campus.

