**Sample size**

The sample size for this study is based upon feasibility and review of similar studies. The literature demonstrates that feasibility studies with similar interventions and methodologies within the cancer population recruit on average 40 participants in total (Eyles *et al.* 2015; Victorson *et al.* 2017; Price-Blackshear *et al.* 2020). Therefore it is anticipated that this study will recruit a total of 40 participants with 20 in each arm of the study.

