**Statistical methods**

Descriptive statistics will be performed to produce mean values and standard deviations. Groups will be compared at baseline using independent t-test (two independent samples) for continuous data, and the chi-square test for independence for categorical data.

Primary analyses will be performed using the intention to treat on all data and using imputation method where outcomes are missing. Alpha will be set a priori at a level of P = .05. Repeated-measures ANOVAs will then be used to determine the effects of exercise and mindfulness and mindfulness intervention on changes in all outcomes of interest.

As this is a feasibility study and preliminary efficacy study, effect sizes (Cohen’s d) will be calculated by taking the mean difference and dividing by the pooled standard deviation to better estimate the meaningfulness of change for each observed outcome following the intervention. The values and meanings for effect size estimates are a small effect size (d = .2), a moderate effect size (d = .5), and a large effect size (d = .8).

Corelation analysis will be performed to determine whether changes in mindfulness/exercise are associated with changes in fatigue, anxiety, depression or sleep.

References.

Craig, P.e.a. (2019) Medical Research Council Developing and
evaluating complex
interventions.

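### Both arms receive mindfulness, so randomisation supports only the added effect of exercise; the need statement, the secondary aim and the stated purpose of the ANOVAs claim more

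*Protocol*

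**What the plan says.** Need for a trial names as unexplored: "Whether mindfulness and indeed adding mindfulness to an exercise regime for managing fatigue in women with gynaecology cancer is of benefit". It then sets the study to assess feasibility and acceptability, and "if there is any effect on fatigue for the gynaecology cancer patient".

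The primary aim is feasibility: "To explore the feasibility of conducting an 8- week online mindfulness and home-based walking and strength training programme". The secondary aim is clinical: "To evaluate the effect of an 8 week exercise and mindfulness programme on cancer related fatigue as a primary clinical outcome". It names no comparator.

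Study design describes an open trial with "1:1 allocation to either the mindfulness only group or the exercise and mindfulness group". No arm receives exercise alone, and none receives neither component. The title does name the comparison that these arms make: "evaluating the effectiveness of mindfulness compared to exercise and mindfulness on fatigue in women with gynaecology cancer".

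Statistical methods sets alpha at .05 and says that repeated-measures ANOVAs will establish the effects of both the combined programme and the mindfulness programme on change in every outcome. Cohen's d is a mean difference over a pooled standard deviation, intended "to better estimate the meaningfulness of change for each observed outcome following the intervention". The sentence does not say whether the difference is between arms or between time points.

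**The concern.** Three places state an effect that the arms do not isolate. The need statement asks about mindfulness, and about mindfulness added to exercise, whereas the design adds exercise to mindfulness. The secondary aim can be read as the effect of the whole programme against nothing. Statistical methods expects the ANOVAs to deliver an effect of mindfulness, although nobody goes without it.

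An effect of mindfulness, or of the programme as a whole, could come only from change over time. That change also contains whatever would have happened anyway:

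- recovery, since entry is allowed from 3 months after treatment;
- regression to the mean, since entry requires a fatigue rating of at least 4 on 0-10;
- weekly contact with the researcher, given with both interventions;
- expectation, in an open trial with self-reported outcomes.

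Statistical methods describes the study as partly one of preliminary efficacy. An uncontrolled change reported as benefit could therefore be carried into the effect size assumed for a later trial.

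**Working it through.** **Sample size.** The plan's figure is 40: "this study will recruit a total of 40 participants with 20 in each arm of the study", and 2 × 20 = 40. It is based on similar feasibility studies, with no effect size or SD, so there is no power calculation to reproduce.

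**What the arms identify.** Let the mean outcome be μ with neither component. Let m be the effect of mindfulness, e the effect of exercise, and i their interaction.

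- Mindfulness only: μ + m
- Exercise and mindfulness: μ + m + e + i
- Difference (second minus first): e + i

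A contrast can be estimated without bias from the two arms only if it is a linear combination of the design rows (1,1,0,0) and (1,1,1,1). A rank check gives:

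| Question | Contrast | Identified? |
|---|---|---|
| Exercise added to mindfulness | e + i | Yes |
| Mindfulness alone | m | No |
| Mindfulness added to exercise | m + i | No |
| Whole programme against nothing | m + e + i | No |

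The third row would need an exercise-only arm. The second and fourth would need an arm with neither component.

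**What the ANOVA contains.** With two arms and two assessments (baseline and end of programme), the arm-by-time term estimates e + i and is a randomised comparison. The time term is average change across both arms and has no control.

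**Illustration of the time term.** This applies only if that term is read as efficacy.

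- From the protocol: 40 participants and about 20% attrition, so 40 × 0.8 = 32 completers; alpha .05. Sidedness is not stated. Two-sided is assumed, which leaves 2.5% in the favourable direction.
- Assumed, because the protocol gives neither: drift δ of 0.1, 0.2 or 0.3 SD unrelated to the programme, and a baseline-to-follow-up correlation ρ of 0.6, varied from 0.4 to 0.8.

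Treat the time effect as a paired comparison. The standardised change is dz = δ / √(2(1 − ρ)) and the noncentrality is dz × √32, on 31 degrees of freedom with critical t = 2.04. At ρ = 0.6, √(2 × 0.4) = 0.894, so:

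- δ = 0.1: dz = 0.112, noncentrality 0.63, probability 8.9%
- δ = 0.2: dz = 0.224, noncentrality 1.26, probability 23%
- δ = 0.3: dz = 0.335, noncentrality 1.90, probability 45%

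Sensitivity, for δ = 0.1 / 0.2 / 0.3:

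- ρ = 0.4, n = 32: 7% / 17% / 32%
- ρ = 0.8, n = 32: 14% / 41% / 74%
- ρ = 0.6, n = 40 (everyone analysed, closer to the stated intention-to-treat analysis with imputation): 10% / 28% / 54%

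**The case against.** The strongest reply is that the analysis already contains the right comparison. A repeated-measures ANOVA on two randomised arms has an arm-by-time term, and the protocol does not say that the time term will carry the inference. A mean difference over a pooled SD is the usual two-group form of d, and a change following the intervention is compatible with a between-arm difference in change. This stands. A reader might infer that the planned ANOVA and d can deliver only before-after change, but the text does not support that: the ANOVA includes a valid contrast, and d is ambiguous.

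The title also names the correct comparison, and read alongside it the secondary aim could mean the effect relative to mindfulness alone. The need sentence is background, and the primary aim and outcomes concern feasibility. These points limit the weight of the concern. They do not make an effect of mindfulness identifiable, and Statistical methods says that the ANOVAs will establish one.

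The sources of drift can be overstated. Selection uses a 0-10 rating at screening, whereas the outcome is baseline FACIT-F, a different instrument completed later, so some regression may already have occurred. The entry window extends to 5 years after treatment, so recovery need not be marked. Both points bear on the size of the drift, which is unknown.

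A reader might also take 9% to 45% as this trial's false-positive rate. It is not. The figures depend on assumed drift and correlation, and on the time term being reported as efficacy, which the protocol does not say will happen.

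**Conclusion.** The concern holds in a limited form. The two arms identify the effect of exercise given mindfulness and no other effect of the components. The need statement, the secondary aim read as the whole programme, and the stated purpose of the ANOVAs claim effects outside that. This follows from the arms alone and needs no numerical assumption.

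It is more than detail left to an analysis plan, because the protocol itself states the question, the aim and what the ANOVAs are to show. Followed literally, it would credit uncontrolled change over time to mindfulness or to the programme at alpha .05. The possible size, 9% to 45% at a correlation of 0.6 and about 7% to 74% over correlations of 0.4 to 0.8, against a nominal 2.5%, is illustrative and conditional as set out above.

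The correction should be made, but it concerns the secondary clinical outcomes only. It does not undermine the feasibility aims, the arms or the sample size.

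**What to change.** 1. In Need for a trial and the secondary aim, state the clinical question as the preliminary effect on fatigue, and on the other clinical outcomes, of adding exercise to mindfulness. Remove or reverse the question about adding mindfulness to exercise.
2. In Statistical methods, state that the arm-by-time (between-arm) contrast, exercise and mindfulness minus mindfulness only, is the clinical effect estimate, and that Cohen's d is computed on it.
3. Report within-arm change descriptively, with confidence intervals and without a claim of benefit.

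These are wording changes. The arms, the 40 participants, the assessments and the feasibility outcomes stay as they are. The cost is a narrower claim: the trial would say nothing causal about mindfulness itself or about the programme as a whole.
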